## Abstract

**Introduction:**

An elevated postprandial glucose response is associated with an increased risk of cardiometabolic diseases. Existing research suggests large heterogeneity in the postprandial glucose responses to identical meals and food products between individuals, but the effect of other consumed meals during the day and the order of meals during the day on the heterogeneity in postprandial glucose responses still needs to be investigated. In addition, the robustness of the glucose responses to meals or foods is still unknown.

**Objectives:**

The overall aim of the project is to assess whether the glucose response to a meal is sufficiently person-specific to use in personalized dietary advice. We aim to answer the question: “How replicable are glucose responses to meals within individuals and how consistent is the variation in glucose responses between individuals?”

**Methods:**

The question will be assessed under standardized conditions of a 9-week fully controlled dietary intervention in which all meals are the same between individuals and consumed in a fixed order at a fixed time. 63 apparently healthy men and women with a BMI of 25–40 kg/m^2^ and aged 45–75 years were enrolled in the RepEAT study (NCT05456815), of whom 53 participants completed the study. The RepEAT study comprised a fully controlled dietary intervention of nine weeks, consisting of three repetitive periods of three weeks. Within each three-week period, a variety of meals and food products were offered during breakfast, lunch, dinner and in between meal snacks. Throughout the dietary intervention, glucose was continuously monitored using Freestyle Libre Pro IQ monitors. Physical activity was monitored using the ActiGraph and ActivPAL. To measure the association between glucose responses and an individual’s phenotype, various measurements were performed before the start of the dietary intervention including an oral glucose tolerance test, a high-fat mixed meal challenge, assessment of body fat distribution including liver fat (MRI/MRS), and cardiometabolic markers.

**Discussion:**

The repetitive and fully controlled nature of the dietary study allows detailed assessment of the replicability of the glucose responses to meals and food products within individuals. Furthermore, the consistency of the variation between individuals independent of insulin resistance will be determined.

## Introduction

1

The incidence of chronic metabolic diseases and associated healthcare costs are rising worldwide, and despite considerable attention, are expected to further increase in the coming decades (1). A common consequence of obesity and an early feature of chronic metabolic diseases is impaired glucose homeostasis as shown by elevated fasting or postprandial glucose levels (2). Elevation of postprandial glucose responses is indicative of insulin resistance and impaired glucose tolerance and is associated with an increased risk of the development of diabetes (3, 4). To correct and prevent impaired glucose homeostasis, a combination of diet- and lifestyle interventions is recommended. General dietary guidelines aim to promote health and reduce the risk of chronic metabolic diseases such as diabetes among the general adult population (5). However, although adherence to the general dietary guidelines will reduce disease risk at a population level, the current “one-size-fits-all” strategy may not provide optimized dietary advice at the individual level, by failing to take into account inter-individual differences in response to diet and meals.

Existing research shows a large heterogeneity in the plasma response to meals. Zeevi and colleagues (6) studied the variation in postprandial glucose responses in a cohort study (*n* = 800) using continuous glucose monitors. Participants followed their habitual diet and recorded consumed meals and food products in a food diary. The study showed marked variation in postprandial glucose responses between individuals to similar meals. Data of this study was used to develop an algorithm that could predict postprandial glucose responses based on physiological characteristics. The algorithm was validated in a separate cohort (*n* = 100) and dietary advice based on this algorithm could reduce postprandial glucose responses in another 26 participants. In an American cohort, the same algorithm could more accurately predict postprandial glucose responses compared to regular approaches based on nutritional content only (7). Moreover, the study of Zeevi and colleagues in 800 individuals (6) reported highly divergent responses between individuals as illustrated by one participant showing a high glucose response to a banana but not to a cookie, whereas another participant showed a high glucose response to a cookie but not a banana. Similarly, the same research group found highly divergent responses to sourdough and white bread among 20 healthy individuals (8). Collectively, these findings suggest that there might be a person-specific postprandial glucose response to meals.

More recently, Berry and colleagues (4) similarly investigated the variation in postprandial glucose responses between individuals. In this cohort study of 1,002 healthy adults, numerous baseline measurements were performed, after which glucose concentrations were continuously monitored for two weeks. Participants followed their habitual diet and consumed several standardized meals of different macronutrient compositions. The study revealed a high heterogeneity in postprandial glucose responses between individuals. Postprandial glucose responses could be predicted by a machine-learning model based on genetics, meal macronutrient composition, meal timing, sleep, exercise, and faecal microbiome composition. In addition, insulin sensitivity will affect glucose responses (9) and other physiological factors such as physical activity (4, 10) and sleep (4, 11, 12) could also influence postprandial glucose responses.

The studies of Zeevi and Berry and colleagues have revealed substantial variations in the glucose response to self-reported and standardized meals between individuals. However, several factors that may have affected the glucose responses remain to be explored. First, the time between the meal of interest and the previous meal may play a role in the glucose response. This was clearly shown in the study of Berry and colleagues (4), in which two identical meals were provided at breakfast and lunch, which resulted in a significantly higher average glucose response to the second meal at lunch compared to the first meal after an overnight fast. Standardized conditions throughout the day are essential to determine whether the glucose response to a meal is person-specific or due to consumption during a different time of the day, e.g., during breakfast or lunch. Second, previous research suggests the presence of a second-meal effect (13, 14), which is the effect of the composition of the previous meal on the next meal. Third, assessing food intake through a food diary gives a broad overview of the consumed foods, but differences in food products are not recorded. For instance, the ripeness of a banana is not recorded but may influence the postprandial glucose response. A fully controlled standardized diet with repeated consumption of the same meals and foods at a fixed time and order is essential to reliably determine person-specific postprandial glucose responses to meals, which is necessary for accurate personalized dietary advice.

The RepEAT study was designed to take all these factors into account. The overall aim of the study is to assess whether the glucose response to a meal is sufficiently person-specific to use in personalized dietary advice. We aim to answer the following question: “How replicable are glucose responses to meals within individuals and how consistent is the variation in glucose responses between individuals under standardized conditions of a 9-week fully controlled dietary intervention?”. More specifically, for example, we will answer the question: “Do individuals, compared to their average glucose response over nine weeks, replicably show large postprandial glucose responses following consumption of certain foods, whereas other individuals replicably show large postprandial glucose responses following consumption of other foods?”. In addition, we aim to examine if this variation in glucose responses is related to an individual’s phenotype.

## Methods

2

### Study design

2.1

The RepEAT study was a fully controlled dietary intervention trial carried out at Wageningen University & Research (WUR), Netherlands. The study was conducted between August and December 2023, and the project is currently in the phase of data cleaning. The study was approved by the Medical Ethics Committee Oost-Nederland, Netherlands (NL80179.091.21) and was registered at ClinicalTrials.gov (NCT05456815). The RepEAT study was conducted according to the Declaration of Helsinki (15), and all participants signed a written informed consent prior to the start of the study.

This fully controlled dietary trial consisted of a 9-week dietary intervention (Figure 1). The primary outcome of the study is the person-specific glucose responses as measured by the 2 h incremental area under the curve (iAUC). Glucose responses will be measured using continuous glucose monitoring. Glucose was continuously monitored throughout the 9-week dietary intervention to determine glucose responses to all food products and meals during the intervention. To prevent an effect of preparation of meals on the glucose response, all meals and food products were prepared and provided by the research facility. To enable the assessment of postprandial glucose responses to all meals and food products without interference of other meals, all meals and food products were consumed according to a fixed schedule with at least a two-hour interval between all meals and snacks. Physical activity was continuously monitored throughout the dietary intervention to assess physical activity patterns. To determine potential associations between an individual’s phenotype and their postprandial glucose response, participants were comprehensively characterized before the start of the dietary intervention. To assess whether consumption of a controlled diet for nine weeks reduced the overall variation in these characteristics, some of the baseline measures were repeated at the end of the dietary intervention (Figure 1).

**Figure 1 fig1:**
[figure not shown]
Design of the RepEAT study. In a characterization period, phenotype was identified. Afterwards, participants followed a 9-week fully controlled dietary intervention in which glucose concentrations and physical activity were continuously monitored. The dietary intervention consisted of three repetitive periods of three weeks. At the end of the 9-week dietary intervention, some of the measurements were repeated. The blue circles indicate the sample frequency. CANTAB, Cambridge neuropsychological test automated battery; HFMM, high-fat mixed meal; MRI, magnetic resonance imaging; ^1^H-MRS, proton magnetic resonance spectroscopy; OGTT, oral glucose tolerance test.

#### Study participants

2.1.1

Participants were recruited from a volunteer database of the Division of Human Nutrition and Health, a commercial database and via local and online advertisements and distributed flyers in Wageningen and surroundings. Apparently healthy individuals were included if they were aged between 45–75 years, had a body mass index between 25–40 kg/m^2^, and were weight stable, meaning <3 kg fluctuation in the two months prior to the screening. Exclusion criteria were among others: diagnosis of diabetes mellitus type I or type II; medication interfering with glucose metabolism and/or immune function; diseases or prior surgeries affecting the stomach, liver, or intestine; food allergies/intolerances for products used in the study design; dietary habits interfering with the study; anaemia defined as Hb concentrations <8.5 mmol/L for men and < 7.5 mmol/L for women; and veins not suitable for a venflon needle. A complete list of inclusion and exclusion criteria is provided in Supplementary Table S1. During the screening visit eligibility was assessed, where individuals filled out questionnaires to check inclusion and exclusion criteria. Hb concentrations were measured with a point-of-care finger prick test and the suitability of veins was assessed by a research nurse.

#### 9-week controlled diet

2.1.2

The 9-week diet followed the average dietary pattern of middle-aged men and women in the Netherlands according to the Dutch National Food Consumption Survey 2012–2016. The 9-week diet was designed to maintain a stable body weight, and was not designed to induce any phenotypical changes in an individual. The diet was calculated for eight energy groups ranging from 7–14 MJ / 1,600–3,400 kcal to maintain body weight stability throughout the dietary intervention. The total energy content was adjusted to energy requirements, but was similar in macronutrient composition for all energy groups, i.e., all energy groups received the same energy percentage of each macronutrient.

To design the menu cycle, first the requirements of the diet were specified, including products and meals of interest, restricted time schedules, and portion sizes. These requirements were used in a tailored version of a mixed-integer linear programming model (16) to generate a menu cycle that complied with all constraints. The nutritional composition of the diet was calculated using the Dutch Food Composition Database (NEVO-online version 2021/7.1, RIVM, Bilthoven, Netherlands). The dietary intervention consisted of three repetitive periods of three weeks. Consequently, all food products and meals were given at least three times. Within each three-week period, different versions of the same food product and meal were given at the same eating moment. For instance, participants consumed whole grain wheat bread, refined grain wheat bread, and sourdough bread on the same weekday and the same time of day.

Before the start of the dietary intervention, participants filled out a Food Frequency Questionnaire (FFQ) (17). The results of the FFQ in combination with the Schofield equations (18) were used to estimate a participant’s habitual energy intake and basal metabolic rate, respectively. Based on these calculations, participants were allocated to one of the eight energy groups to maintain body weight stability. To further support weight stability, research dieticians recorded the body weight of participants twice a week. If necessary, participants switched to a higher or lower energy group to remain weight stable.

In total, 90%–95% of the diet was provided by the research facility. To enhance compliance by giving participants some autonomy, 5%–10% of the diet was part of a “point system” in which participants chose products from a provided list. The food products mainly consisted of products high in mono- and disaccharides and/or containing alcohol. The amount of food that needed to be consumed was dependent on the energy group, and all food products reflecting the “points” had to be consumed within a set timeframe of one hour. Participants recorded all food products that were consumed using the “point system.” All food products and meals were provided in meal packages for at-home consumption, except for the food products from the point system. The participants received meal packages prepared and provided by the research facility. Twice a week, the participants visited the research facility for a joint dinner to enhance compliance, to provide room for questions and to monitor body weight. In addition, some food products were consumed in group video calls to ensure the food products were consumed at the scheduled time.

#### Food products and meals

2.1.3

To measure the variation in postprandial glucose responses to different food products or meals, we selected a specific set of food products and meals to become incorporated into the controlled diet. These products varied each week in the three-week menu cycle and were selected based on previous literature (4, 6, 8) and societal relevance. For instance, we aimed to assess the variation in glucose responses to whole grain wheat bread, refined grain wheat bread, and sourdough bread. We also aimed to examine the variation in glucose responses to single food products, such as potato chips, chips from potato powder, and popcorn. The food products and meals that were directly compared, were consumed at the same weekday and the same time of day. For all selected products, either the carbohydrate content or the meal size remained similar; for potato chips, chips from potato powder, and popcorn, the carbohydrate content was kept comparable between the products, whereas for the different bread types the number of slices of bread was kept the same.

We also included products that were reformulated to be reduced in sugar content and/or glycaemic index. Within a product category, a reference product and two reformulations were tested within a three-week period, which was copied exactly in the second and third three-week period. Per reference/reformulated product, we once measured plasma glucose and insulin concentrations before and 2 h after consumption. To examine the relationship between consumption of the reformulated foods, glucose response, and perceived well-being, well-being was measured by a questionnaire before and 1, 2, and 4 h after consumption of the reformulated or reference products. Well-being was assessed by the adjusted Multidimensional Mood Questionnaire (MDMQ) (19), asking for fatigue, satisfaction, calmness, energy, the feeling of fitness, and tenseness on a visual analogue scale.

#### Glucose monitoring

2.1.4

During the characterization and throughout the 9-week dietary intervention, interstitial glucose concentrations were continuously monitored using the Freestyle Libre Pro IQ (Abbott, Chicago, United States). The sensors of these continuous glucose monitors could store data for two weeks without exporting data to a reader. In addition, the glucose concentrations were blinded for participants which prevents participants to change their diet/consumption patterns based on their postprandial glucose responses. Sensors were replaced every two weeks, and although the diet remained controlled, no specific test products were planned one day after the replacements to let the sensors stabilise.

Postprandial glucose responses will be calculated as the incremental area under the curve (iAUC) from the earliest time point before the start of a meal until 2 h after the meal. In addition, the maximum glucose value and time to peak will be calculated using the most recent version of R. Next to the postprandial glucose response, the variation in glucose concentrations across the whole dietary intervention and over each three-week period will be determined. To calculate the variation over the nine-week and three-week periods, glucose concentrations over the respective period will be used to calculate outcomes of glucose variability, as reviewed by Rodbard (20): coefficient of variation (CV), standard deviation (SD), mean amplitude of glycaemic excursions (MAGE), mean absolute difference (MAD), and mean of daily differences (MODD).

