## Statistical analysis

3

Within the RepEAT study, we aim to examine how replicable glucose responses are within individuals and how consistent the variation in glucose responses is between individuals under standardized conditions of a 9-week fully controlled dietary intervention. To determine the replicability of glucose responses to identical meals and food products within individuals, we will compare the three repetitions per meal or food product. To assess the variability in glucose responses to identical meals between individuals, we will compare the three repetitions per product between individuals. Glucose responses will be corrected for metabolic state of insulin sensitivity by using the average glucose response to all meals in the diet and/or the glucose response to the OGTT, and by correcting for physical activity.

IBM SPSS Statistics and the latest R software will be used to carry out the statistical analyses. Numerical values in descriptive statistics will be reported as mean ± SD, categorical values will be reported as numbers and percentages. To determine the normality of the data, a visual inspection of QQ plots and results of the Kolmogorov–Smirnov test will be used. For linear mixed model analyses, model residuals will be checked for normality. Non-normally distributed data will be transformed before the analyses. *p*-values <0.05 will be considered statistically significant.

Glucose responses to single meals will be measured as the incremental area under the curve (iAUC; mg/dl*hour) and will be calculated from the latest timepoint before consumption until 120 min after consumption. In addition, the glucose peak and time to peak will be measured within each postprandial glucose response curve, within 120 min after consumption of a test product. For each meal and food product there will be three repeated measures during the dietary intervention. Glucose responses to single meals will be associated with the average iAUC of all glucose responses of an individual. There will be adjusted for multiple testing using false-discovery rate adjustment according to the Benjamini-Hochberg procedure (32).

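### The three analysed repetitions of a meal always fall on different glucose sensors, so comparing them directly counts sensor gain differences as within-person non-replicability

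*Protocol article*

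**What the plan says.** All references are to the protocol article.

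- **Sensors (2.1.4, Glucose monitoring).** On storage: "The sensors of these continuous glucose monitors could store data for two weeks without exporting data to a reader". On replacement: "Sensors were replaced every two weeks, and although the diet remained controlled, no specific test products were planned one day after the replacements". The stated reason is to let the new sensor settle. This is the only provision about sensors.
- **Diet (2.1.2).** "The dietary intervention consisted of three repetitive periods of three weeks". The Discussion calls the three periods identical. For reformulated products, section 2.1.3 describes a three-week set "which was copied exactly in the second and third three-week period".
- **Number of repetitions.** Section 3 states: "For each meal and food product there will be three repeated measures during the dietary intervention". Section 2.1.2 words it as a minimum: "Consequently, all food products and meals were given at least three times".
- **Analysis (3, Statistical analysis).** For replicability within individuals, "we will compare the three repetitions per meal or food product". The named corrections are the average response to all meals and/or the response to the oral glucose tolerance test, together with physical activity. Linear mixed models are mentioned, but their terms are not listed. Single meals are also related to a mean iAUC taken over every response of the person.

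**The concern.** Replicability within a person is the first half of the study question. If repetitions of a meal are always read by different devices, their spread contains two things: real change in the person's response, and differences between devices. A direct comparison treats both as the person failing to replicate. The error has one direction, because device variance can only add to the within-person term. The same noise would also weaken the correlation between a meal and the person's average, which section 2.4 reads as a sign of a person-specific response.

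A smaller point concerns the day after each replacement. The plan keeps test products off that day, yet the average iAUC is defined over all responses and the variability indices over the glucose values of the whole period. No exception for that day is stated.

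**Working it through.** **Inputs from the article.** Sensor interval 14 days (2.1.4). Cycle 21 days, three cycles, 63 days (2.1.2). Meals per completer 378 (Results), which gives 378/63 = 6 per day and 378/3 = 126 per cycle. The plan states no figure on this point to reproduce.

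**1. Do repetitions share a sensor?** Repetitions fall on days d, d+21 and d+42. Sharing would need a sensor worn for more than 21 days. Enumerating 14 possible sensor start days x 21 menu days x 3 pairs gives 882 pairs, of which 0 share a sensor. If the first sensor starts on day 1:

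| Menu week | Sensors for repetitions 1, 2, 3 |
|---|---|
| 1 | 1, 2, 4 |
| 2 | 1, 3, 4 |
| 3 | 2, 3, 5 |

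For contrast, product variants compared within one cycle lie 7 or 14 days apart. Of those pairs (14 start days x 7 weekdays x 3 cycles x 3 pairs = 882), 294 (33%) share a sensor.

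**2. Which sensor errors reach the iAUC?** On an illustrative two-hour curve the iAUC is 26.2. Adding 10 mg/dl throughout leaves it at 26.2. A 10% gain error gives 28.9, which is the full 10%. Offsets therefore cancel and gain differences do not.

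**3. Can the named adjustments remove gain differences?** The average response and the tolerance test response are each one value per person, so they are constant across the three repetitions. Physical activity carries no information on the sensor.

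**4. Size.** On the log scale, response = meal + sensor + residual, with sensor effects independent. The repetitions use three sensors, so within-person variance = sensor variance + residual variance, and the sensor share is s²/(s² + e²). The documents give neither s nor e. Over assumed ranges:

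| Sensor SD s | e = 0.20 | e = 0.30 | e = 0.40 |
|---|---|---|---|
| 0.05 | 5.9% | 2.7% | 1.5% |
| 0.10 | 20.0% | 10.0% | 5.9% |
| 0.15 | 36.0% | 20.0% | 12.3% |
| 0.20 | 50.0% | 30.8% | 20.0% |

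Take a between-response SD of 0.30 (also assumed), so a variance of 0.09. At s = 0.15 and e = 0.30 the intraclass correlation falls from 0.09/(0.09 + 0.09) = 0.50 to 0.09/(0.09 + 0.1125) = 0.44 (0.45 in simulation). The largest fall in the range, at s = e = 0.20, is from 0.09/0.13 = 0.69 to 0.09/0.17 = 0.53.

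**5. Can the sensor component be estimated?** A full-length sensor covers 14 x 6 = 84 eating occasions, and sensors straddle the cycles. With 126 meals and 5 sensors, the person-level design has rank 130 = 126 + 4, which is full. In simulation at s = 0.15 and e = 0.30, the within-person variance was 0.111 without the sensor term and 0.089 with it, against a true residual variance of 0.090. No drift over time was simulated.

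**6. Settling days.** About 4-5 replacements in 63 days, so 4/63 to 5/63, or 6-8% of days.

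**The case against.** The strongest objection is that the article fixes no replicability model and may leave its terms to an analysis plan that is not shown. This stands in part. A reader might infer that the authors wrongly left sensor out, and the documents do not support that. What the article does fix is the schedule, the comparison of repetitions and the adjustments it names, and these together put sensor differences into the repetition variance.

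The second objection stands in full: each participant wears one sensor per consecutive 14-day block, so sensor cannot be told apart from calendar block. A sensor effect would also absorb slow physiological drift and part of any switch of energy group. A reader might take the figure with the sensor component removed as true replicability, but it may be too high. The simulation does not test this.

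Third, the target is debatable. Replicability as measured across sensors is a defensible quantity for dietary advice. That is a reason to report both figures, not to replace one with the other.

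Three further inferences go too far:

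- That differences in glycaemic variability between three-week periods would mostly reflect sensors. This does not follow. With an assumed true CV of 0.20 and two sensors whose gains differ by 10%, weighted 2/3 and 1/3, the CV index moves only from 0.200 to about 0.205. The article also specifies no test between periods.
- That dividing each iAUC by its sensor's mean would solve the problem. Sensors cover different menu weeks (with a day-1 start, sensor 1 covers weeks 1 and 2, sensor 5 only week 3), so identical meals would be divided by means of different menus.
- That no two servings of any food ever share a sensor. The minimum of three servings leaves room for extra ones that could. The result holds for the three analysed repetitions.

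The contrast with product comparisons is also modest, since 588 of 882 variant pairs (67%) lie on different sensors too. On the settling days, silence does not prove that they will be kept, since data cleaning was still under way, and no bias from them has been quantified.

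**Conclusion.** The concern holds in this form. The separation of repetitions across sensors is exact for every sensor start day, and it depends only on the 14-day and 21-day intervals. With the adjustments named in section 3 alone, sensor gain variance enters the within-person term in full and lowers apparent replicability.

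The size cannot be taken from the documents. It is about 1.5% to 50% of within-person variance under the assumed SDs, so it may be negligible or material. It also rests on independent sensor gains and a log-scale model. Because the size is unknown and the component can be estimated from data already held, it should be estimated and reported. The settling-day point is minor.

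**What to change.** - On a log or similar scale, fit meal plus a random effect for sensor nested in participant, and report the sensor variance separately from the residual repeat variance.
- Report replicability twice: once with the sensor component counted as within-person variation, and once with it removed. State that sensor is aliased with the 14-day block. Subject to the model and sampling error, the two figures then bracket true replicability: the first is too low if sensors differ in gain, the second too high if people drift.
- Exclude the day after each sensor replacement from the average iAUC and the variability indices, or show results both ways.

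The cost is one random effect, which needs the sensor change dates, and one exclusion rule that removes about 4-5 of 63 days from the summaries. No test product is lost, because none was planned on those days.
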